## SMART Design

A Sequential Multiple Assignment Randomized Trial (SMART) design is a multistage trial methodology specifically developed to inform the construction of effective adaptive interventions[28–31]. Adaptive interventions are sequences of decision rules that recommend when and how to modify interventions based on individuals' characteristics and evolving response to treatment. Unlike traditional randomized controlled trials (RCTs) that evaluate fixed interventions, SMART designs enable researchers to systematically test critical questions in the development of adaptive interventions, particularly questions about treatment sequencing and individualization[29].

The SMART design is particularly appropriate for our research objectives for several reasons:

### Addressing Heterogeneity in Treatment Response

Mild cognitive impairment (MCI) patients demonstrate significant heterogeneity in disease progression, cognitive profiles, and responses to interventions[32]. Current evidence suggests that the optimal sequence and dosage of interventions vary substantially among individuals, with important implications for intervention effectiveness. The SMART design explicitly addresses this heterogeneity by enabling evaluation of multiple intervention pathways tailored to individual response patterns.

For example, as shown in our preliminary data, participants with different baseline cognitive statuses and comorbidity profiles respond differently to VR-based Taichi versus conventional Taichi. A SMART design allows us to systematically investigate these differential response patterns and develop evidence-based rules for matching patients to the most beneficial intervention sequences.

### Enabling Dynamic Decision-Making

MCI management requires making sequential treatment decisions over time, particularly as patients' cognitive status changes[33,34]. The SMART design mirrors this clinical reality by incorporating decision points where intervention strategies can be modified based on interim outcomes. This approach allows us to answer critical questions about when to intensify, switch, or maintain interventions based on early response indicators.

Specifically, our design includes an assessment of intervention mastery at week 12, with non-responders being re-randomized to either alternative interventions (switching from offline Taichi to VR Taichi or vice versa) or intensified interventions (doubled doses). This mirrors clinical practice where practitioners typically adjust treatment approaches when patients show insufficient progress.

### Identifying Optimal Treatment Sequencing

The optimal ordering of multicomponent interventions is a critical but understudied aspect of MCI management. A SMART design can determine whether treatment sequences matter - for instance, whether initiating with VR Taichi followed by offline Taichi for non-responders produces different outcomes compared to the reverse sequence.

This is particularly relevant given recent evidence suggesting potential synergistic effects between different intervention modalities. For example, Boa Sorte Silva et al. (2024) and has demonstrated that combined exercise and cognitive interventions may yield greater benefits than single-component interventions[35].

### Overcoming Limitations of Traditional Methodology

Conventional approaches to studying adaptive interventions have significant limitations that SMART designs overcome:

1. **Observational studies** that inform current adaptive intervention practices lack the randomization necessary for causal inference, making their findings vulnerable to confounding.
2. **Multiple single-stage RCTs** conducted in sequence would require substantially more participants, time, and resources than an integrated SMART. Moreover, they would fail to capture the important interaction effects between sequential treatments that may influence long-term outcomes.
3. **Standard factorial designs** are inefficient for studying adaptive interventions as they do not account for the time-varying nature of treatment decisions and cannot easily incorporate response-contingent treatment adaptations.

### Integration with Causal Discovery Methods

Our study innovatively integrates SMART with causal discovery methods to develop a causality-driven dynamic treatment regime framework (cDTR-SMART). This methodological approach enhances model generalizability by explicitly accounting for underlying causal mechanisms while effectively capturing complex non-linear relationships between intervention intensities.

This integration addresses key limitations of conventional SMART analyses:

1. It reduces the effective dimensionality of the problem, enabling valid inference with smaller sample sizes - particularly important for MCI research where large-scale recruitment can be challenging[36].
2. It captures complex, non-linear dose-response relationships in multicomponent interventions that linear models might miss.

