
### Added value of this study

This study represents the first exploration of adaptive optimal intervention strategies in MCI management through a causality-driven dynamic treatment regime framework by sequential, multiple assignment, randomized trial (cDTR-SMART). The cDTR-SMART is a generalizable computational framework for deriving adaptive optimal intervention strategies, which integrates Peter-Clark causal discovery algorithms to identify influential causal pathways and incorporates them into a state space model, ultimately utilizing reinforcement learning to determine optimal action spaces across different states.

In our analysis of participants, we identified cognitive status, age, and presence of diabetes and hypertension as key state space variables, which enabled the derivation of personalized optimal intervention combinations (Virtual reality Taichi, Offline Taichi, Cognitive function training) through our reinforcement learning model. The study revealed substantial individual heterogeneity in treatment responses, with an average treatment effect of 0·587 (95% CI [0·022, 1·152]). Notably, the intervention demonstrated pronounced effectiveness in older participants with lower cognitive states (ITE: 0.94), with this effect further amplified in the presence of chronic conditions (ITE: 1.12), suggesting that the most vulnerable subgroups might benefit most from the intervention. Additionally, SHAP analysis revealed that age demonstrated the most pronounced heterogeneous effects in VR Taichi responses, while diabetes status showed consistently positive clustering of SHAP values for offline Taichi practice, indicating enhanced benefits for participants with metabolic conditions. This data-driven approach transcends the generic non-pharmacological intervention guidelines in current dementia prevention protocols by providing actionable, precise intervention recommendations. Furthermore, by incorporating causal discovery methods, this approach offers interpretable insights into intervention intensity adjustments based on individual patient characteristics, making it both practically applicable and theoretically sound for personalized cognitive intervention.

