## Primary Outcome

The primary outcome is the optimal adaptive intervention strategy derived through reinforcement learning algorithms, quantifying personalized temporal allocations for virtual reality Taichi (VRTC), offline Taichi (OffTC), and cognitive training (CT) in clinically implementable 5-minute intervals.

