## Sample Size and Power Analysis

The study size was determined based on response rate parameters drawing from multicomponent intervention studies and previous response rates. We calculated a required sample of 54 participants in the intervention group (assuming 0.60 response rate, 0.05 type I error, 0.45 half-width confidence interval, and 0.80 statistical power).

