## Vulnerable Populations

## Local Number of Participants

92 participants will be enrolled (approximately 30 each for OffTC+CT and VRTC+CT, and approximately 30 for control).

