**Heterogeneity in Treatment Effects**

We will analyze heterogeneity in treatment effects through:

SHAP value analysis to quantify the impact of participant characteristics on treatment effectiveness

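### Reducing dimension by causal discovery does not by itself give valid inference at this sample size: a policy chosen and judged on the same participants looks better than it is, and SHAP ranks modifiers even when there are none

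*Protocol*

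**What the plan says.** Under *Integration with Causal Discovery Methods*, the protocol gives as the first advantage of its approach: "It reduces the effective dimensionality of the problem, enabling valid inference with smaller sample sizes". It attaches no condition.

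Under *Added value of this study*, the framework "integrates Peter-Clark causal discovery algorithms to identify influential causal pathways and incorporates them into a state space model", after which reinforcement learning derives the actions. The same section reports where the variables came from: "In our analysis of participants, we identified cognitive status, age, and presence of diabetes and hypertension as key state space variables". Individual effects and SHAP patterns follow in the same paragraph.

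Under *Primary Outcome*: "The primary outcome is the optimal adaptive intervention strategy derived through reinforcement learning algorithms". Under *Heterogeneity in Treatment Effects*, the one listed method is "SHAP value analysis to quantify the impact of participant characteristics on treatment effectiveness".

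On size, *Local Number of Participants* says "92 participants will be enrolled (approximately 30 each for OffTC+CT and VRTC+CT, and approximately 30 for control". *Sample Size and Power Analysis* says "We calculated a required sample of 54 participants in the intervention group". The inputs listed there for that figure read: "assuming 0.60 response rate, 0.05 type I error, 0.45 half-width confidence interval, and 0.80 statistical power".

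**The concern.** Fewer variables make a model more stable, but they do not make the inference valid when the data chose them. Three steps compound here. The participants' data pick the state variables, a search over policies picks the one that looks best on those variables, and the benefit is then read off. If all three use the same people, the winner's apparent value includes the noise that made it win.

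SHAP raises a related problem. It decomposes the predictions of a fitted model. A flexible model fitted to noise still varies its predictions across people, so SHAP returns a non-zero, ranked list under a constant effect. It offers no way to tell that case from real heterogeneity.

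The primary outcome is thus an object that the algorithm will always return, whether or not tailoring helps anyone. A reader who takes the sentence at face value would treat it as inferentially sound at this sample size.

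**Working it through.** **Inputs.** From the protocol: 92 participants, about 30 of them controls, so 92 − 30 = 62 on active treatment; response rate 0.60; half-width 0.45; four state variables; two first-stage active arms; non-responders re-randomised between two options. Assumed: outcome SD of 1, binary state variables at 50% prevalence, 1:1 re-randomisation.

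**1. The plan's own figure.** For the mean of one embedded strategy when only non-responders are re-randomised, N = 2(2 − r)(z/h)². With r = 0.60, z = 1.96, h = 0.45 and SD 1, this is 2.8 × 18.97 = 53.1, so 54. The stated number reproduces, although the 0.80 power plays no part in the formula. The trial is thus sized to estimate one strategy mean to within ±0.45 SD. Choosing between strategies, learning a policy and finding modifiers do not enter.

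**2. What 62 people give.**
- Half-width for one strategy mean: 1.96 × √(2.8/62) = 0.42 SD.
- Half-width for a difference between two strategies that start with different arms: 1.96 × √(5.6/62) = 0.59 SD.
- Each re-randomised cell: 31 × 0.40 / 2 = 6.2 people (simulated 95% range 2 to 11).

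**3. Optimism when every true effect is zero (simulated).**
- Best of the four embedded strategies, chosen and judged on the same 62 people: mean apparent gain 0.20 SD.
- Better of two active arms within each of 16 cells (2⁴) of four binary variables: mean apparent gain 0.34 SD. Each cell holds about 62/16 = 3.9 people.

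**4. Does reducing dimension cure it?** A linear rule was fitted to 62 people under the same null. The gain here is on a different scale: the mean of those who happened to receive the recommended arm minus the mean of those who did not.

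| Modifiers in the rule | Apparent gain (SD) | Nominally significant |
|---|---|---|
| 2, fixed in advance | 0.35 | 20% |
| 4, fixed in advance | 0.45 | 40% |
| 4, picked from 8 | 0.56 | 65% |
| 4, picked from 12 | 0.63 | 78% |

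In a new sample of the same size the gain is about zero in every row. Using fewer variables lowers the optimism without removing it, and picking the variables from the data raises it. The number of candidate variables is not given in the protocol, so 8 and 12 are assumptions.

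**The case against.** The strongest reply is that the protocol never says that selection, learning and evaluation share the same people. This is an inference from the section on added value and from the absence of any described split. Fold structure is commonly left to the SAP, which is not at hand. The section on heterogeneity in treatment response also mentions preliminary data on cognitive status and comorbidity, so the candidates may not come only from this sample. All of that stands, and the lack of a described split is not itself the finding. The finding is the unconditional sentence, which holds only under conditions it does not state, together with SHAP as the sole heterogeneity method.

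The second reply is that effects are to be estimated by causal forest double machine learning, which normally cross-fits. This also stands. A reader might infer that the overall average effect is compromised too. It is not: it is a randomised contrast, and the selection problem does not reach it.

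The third reply is that the SHAP section sets no rule for declaring heterogeneity, so nothing false is declared automatically. That is fair, but with no test, nothing in the plan separates signal from noise either.

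The fourth is that the simulations are stand-ins. They are. A reader might also count control as a third option in each of the 16 cells, which gives 0.55 SD, but the primary outcome allocates only the active components. Nor can the reported individual effects of 0.94 and 1.12 be set against simulated subgroup differences. They describe groups defined by several characteristics, on a scale that the protocol does not give.

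**Conclusion.** The concern holds in limited form. The sentence claims a property that the described approach does not have without separate evaluation data. Judged on the data that chose it, with nothing to find, a strategy would look about 0.20 SD better than it is (best of four embedded strategies) to about 0.34 SD better (tailoring on four binary variables). These figures assume unit SD, 62 actively treated people, balanced binary variables and a 60% response rate, and they do not replicate the causal discovery and reinforcement learning pipeline.

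A reader might conclude that the reported optimum and SHAP patterns did arise by chance. The documents and the simulations show only that such patterns can.

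**What to change.** - In *Integration with Causal Discovery Methods*, delete the clause on valid inference with smaller samples, or make it conditional on evaluation in data not used for selection.
- Run variable selection and policy learning inside training folds only. Use repeated cross-fitting: with about 6 people per re-randomised cell, one five-fold split leaves about 6.2/5 = 1.2 per held-out cell.
- Estimate the learned policy's value on held-out data with the known randomisation probabilities. Compare it, with a 95% CI, with the best non-tailored embedded strategy, itself chosen within the training folds. Label the policy exploratory unless that CI excludes zero. The weights exist only for options that were randomised, so state how finer time allocations are valued.
- In *Heterogeneity in Treatment Effects*, add an omnibus treatment-by-covariate interaction test on modifiers fixed without this trial's outcome data, for example from the domains named in *Secondary Aim* (cognitive status, comorbidities, demographics). Do not simply adopt the four variables reported as found in these participants; a test of those would repeat the selection problem. Present SHAP as descriptive only.

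**Cost.** Analysis code and wording, with no new data. Policy value and heterogeneity will look smaller and less certain. The interaction test is weak: with 62 against 30 and a balanced binary modifier, the SE of an interaction is about √[2(1/31 + 1/15)] = 0.44 SD. Simulated power for a test of four modifiers is about 24% for a true interaction of 0.8 SD and 36% for 1.0 SD. A non-significant result is therefore not evidence of no heterogeneity, and the plan should say so.

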## Study Endpoints/Events/Outcomes

## Primary Aim

Determine the optimal adaptive intervention strategy for older individuals with MCI using a causality-driven dynamic treatment regime framework.

## Secondary Aim

Evaluate the average treatment effects (ATE) of different intervention modalities (virtual reality Taichi, offline Taichi, and cognitive training) on cognitive scores measured by Memory Guard.

Analyze heterogeneity in treatment effects across participant subgroups based on cognitive status, comorbidities, and demographic characteristics.

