## Procedures Involved

This study employs a prospective sequential, multiple assignment, randomized trial design. The 24-week SMART design comprises two 12-week phases. In the first phase, eligible participants will be randomly assigned to receive either offline Taichi plus cognitive training (OffTC+CT) or virtual reality Taichi plus cognitive training (VRTC+CT). Each intervention will consist of 1-hour weekly exercise combined with 1 hour weekly cognitive training.

At week 12, participants will be assessed for intervention mastery, with non-responders (defined as those subjectively unable to master the intervention content, scoring less than 3 on a 5-point Likert scale) being re-randomized to alternative or intensified interventions for the second 12-week phase. Responders in Group OffTC+CT will continue their original intervention protocol, while non-responders will be randomly assigned to either VRTC+CT or doubled doses of their original intervention (2OffTC+2CT). Similarly, responders in Group VRTC+CT will maintain their initial protocol, while non-responders will be randomly assigned to either OffTC+CT or doubled doses of their original intervention (2VRTC+2CT). The control group will receive only health education and routine care throughout the 24-week period.

The anticipated duration for individual participation in the study is 24 weeks (6 months). The duration anticipated to enroll all study participants is approximately 9 months (April to December 2023).

[figure not shown]

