### Outcome Assessment

Participants' cognitive function will be monitored using the Memory Guard assessment tool at predetermined intervals (baseline, week 12, and week 24).

[figure not shown]

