## Statistical Considerations

**Average Treatment Effects**

We will use causal forests double machine learning to estimate:

Total ATE between treatment and control groups on cognitive outcomes

Component-specific ATE for VRTC, OffTC, and CT

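### After week 12 only non-masterers switch or double, so week-24 effects by component or hours, and a second-stage policy that ignores mastery, are confounded if mastery is prognostic beyond the listed state variables

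*Protocol*

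**What the plan says.** The Secondary Aim of the protocol asks for the "average treatment effects (ATE) of different intervention modalities (virtual reality Taichi, offline Taichi, and cognitive training" on the Memory Guard score. The Average Treatment Effects section plans, by causal-forest double machine learning, a total effect against control and a "Component-specific ATE for VRTC, OffTC, and CT". The Primary Outcome is a personalised allocation of time to each modality in five-minute steps. The section on causal discovery says the framework captures non-linear dose-response.

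Under Procedures Involved, response at week 12 means mastery. It defines "non-responders (defined as those subjectively unable to master the intervention content, scoring less than 3 on a 5-point Likert scale". Masterers carry on unchanged. In the offline arm, "non-responders will be randomly assigned to either VRTC+CT or doubled doses of their original intervention (2OffTC+2CT"; in the VR arm, "non-responders will be randomly assigned to either OffTC+CT or doubled doses of their original intervention (2VRTC+2CT".

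Memory Guard is measured "at predetermined intervals (baseline, week 12, and week 24". No section says which visit the average treatment effects refer to. On the policy's state, the Added Value section reports that "we identified cognitive status, age, and presence of diabetes and hypertension as key state space variables"; mastery is not among them.

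The Study Intervention section also mentions a step-up for participants who keep declining cognitively. That is a different trigger and must be reconciled with the mastery rule. The point here rests on the mastery rule alone.

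**The concern.** Every crossover, and every hour above the standard dose, belongs to someone who failed the mastery test. Among active participants there is no other source of dose variation. An analysis at week 24 by modality or hours received then compares people selected on a post-randomisation outcome. If non-masterers would score worse anyway, more exposure looks harmful and staying on the first treatment looks beneficial, even when neither has any effect.

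The second randomisation is random only given mastery status and first-stage arm. A policy learned without these in its state would take in the same distortion, and that policy is the primary outcome.

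**Working it through.** **Inputs from the protocol.** Response rate p = 0.60, type I error 0.05, half-width h = 0.45 and a required 54 intervention participants (Sample Size and Power Analysis). One hour of Taichi plus one hour of cognitive training (CT) weekly, in two 12-week phases (Procedures Involved). About 30 participants per group (Local Number of Participants).

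**Assumptions.** The 0.60 is the mastery rate. Re-randomisation is 1:1. h is in SD units and the interval is two-sided. Control hours are zero. The master/non-master gap d, or the correlation behind it, has no source in the documents, so a range is shown.

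**The plan's own figure.** For the mean of one embedded strategy, n = z²[2p + 4(1−p)]/h² = 3.8415 × 2.8/0.2025 = 53.1, rounded up to 54. The figure reproduces without using the stated 0.80 power. It fits reading 0.60 as the rate that decides re-randomisation, and 1:1 allocation.

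**Paths to week 24**

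| Path | Share of arm | VRTC h | OffTC h | CT h |
|---|---|---|---|---|
| VRTC, master | 0.60 | 24 | 0 | 24 |
| VRTC, switched | 0.20 | 12 | 12 | 24 |
| VRTC, doubled | 0.20 | 36 | 0 | 36 |
| OffTC, master | 0.60 | 0 | 24 | 24 |
| OffTC, switched | 0.20 | 12 | 12 | 24 |
| OffTC, doubled | 0.20 | 0 | 36 | 36 |
| Control | 1 | 0 | 0 | 0 |

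**First-assignment contrast.** The VRTC arm averages 0.6×24 + 0.2×12 + 0.2×36 = 24.0 h of VRTC and 0.2×12 = 2.4 h of OffTC; the OffTC arm mirrors it. The own-modality contrast is 24.0 − 2.4 = 21.6 h instead of 24 h, which is 10% smaller if effect is linear in hours.

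**Dose bias with no true effect.** Give masterers mean 0 and non-masterers −d. The doubled group is all non-masterers. The single-dose group holds 0.60 masterers and 0.20 switched non-masterers, so 25% non-masterers. Doubled minus single = −d − (−0.25d) = −0.75d. Switched minus unchanged = −d. Doubled minus switched within non-masterers = 0.

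**Size of d.** For a normal latent mastery scale cut at 60%, d = ρ × 0.3863/(0.6×0.4) = 1.61ρ.

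| ρ | d (SD) | Doubled vs single, −0.75d |
|---|---|---|
| 0.2 | 0.32 | −0.24 |
| 0.3 | 0.48 | −0.36 |
| 0.5 | 0.80 | −0.60 |

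Regressing score on hours in the active arms gives the same answer: covariance −1.44d, variance 23.04, slope −0.0625d per hour, or −0.75d over the 12 h between 24 and 36 h. The slope is equal for VRTC and OffTC hours, so it cancels from their contrast when mastery rates are equal.

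**Controls pooled (equal groups).** Mean hours are 2/3 × 26.4 = 17.6 and the control mean is −0.4d. Covariance = 0.5333×6.4×0.15d − 0.1333×18.4×0.6d = −0.96d. Variance = 103.25 + 21.85 + 45.14 = 170.24. The slope is −0.0056d per hour, or about −0.02, −0.03 and −0.05 SD over 12 h. With mastery in the model the bias is zero.

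**CT.** CT hours equal VRTC plus OffTC hours in every row. Three components span two dimensions, so no separate CT effect can be estimated from these hours, with or without mastery.

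**The case against.** The protocol fixes neither the visit, the exposure coding nor the adjustment set. A causal forest adjusts for covariates, mastery is recorded, and an unseen analysis plan may handle all of this. Comparing sequences is what a SMART is for.

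Much of this stands, and it rules out several stronger readings that a reader might infer:

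- **That week-24 contrasts by first assignment are confounded by non-mastery.** They are not; randomisation protects them. They answer a question about sequences.
- **That VR versus offline Taichi is biased.** The dose slope cancels at equal mastery rates; a bias needs a different mastery mix in the groups compared.
- **That the bias is −0.48, −0.72 or −1.21 SD per 24 h.** This doubles the figures above by extrapolating past the 12 h spread observed. It also comes from an unadjusted, active-only regression that the protocol does not plan.
- **That mastery is certainly absent from the state.** The list is of key variables and may not be complete. Cognitive status, if updated at week 12, could absorb part of what mastery predicts.

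What remains is more than missing detail. The protocol itself names component effects, minutes per modality and dose-response as its targets. Among active participants the design supplies dose variation only through non-mastery.

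**Conclusion.** The concern holds conditionally. A week-24 effect by component or hours received, or a second-stage policy restricted to the listed variables, confounds dose and switching with non-mastery if mastery is prognostic beyond those variables. In the active arms the false dose effect is −0.75d, about −0.24 to −0.60 SD for correlations of 0.2 to 0.5. It falls to roughly −0.02 to −0.05 SD over the same 12 h when controls are pooled. It vanishes when mastery is conditioned on.

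These sizes rest on 60% mastery, 1:1 re-randomisation and an assumed d. The direction needs only that non-masterers have the worse prognosis. First-assignment contrasts at week 24 are valid but diluted to 21.6 of 24 h, so they are not pure modality effects. The separate CT effect is unidentified whatever is done about mastery.

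**What to change.** In Secondary Aim, Secondary Outcomes and Average Treatment Effects:

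1. Define VRTC+CT versus OffTC+CT, and each package versus control, by first-stage assignment at week 12, before anyone has crossed over.
2. At week 24, estimate the four embedded adaptive strategies with weights from the actual re-randomisation ratio (1 for responders and 2 for non-responders if it is 1:1). Do not estimate effects by modality or hours received.
3. Include week-12 mastery and first-stage arm in the second-stage state and adjustment set, whatever the causal-discovery step selects.
4. Drop the separate CT effect, or relabel it as a package effect.

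The cost is wording and analysis only: the week-12 Memory Guard and mastery scores are already scheduled. The pure modality-package effect then covers 12 weeks, not 24. Precision is also modest. With 60 active participants, about 24 are non-masterers, roughly 6 per second-stage cell. The 95% half-width is 1.96×√(2.8/60) = 0.42 SD for one strategy mean, and 1.96×√(5.6/60) = 0.60 SD for a difference between strategies with different first stages.
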